# Annexes

## Annex 9: Questionnaire

Date: DD/MM/YY

### Subject Identification, Clinical and Physical Examination Form

**Title:** *Feasibility, acceptability, safety, and efficacy/effectiveness of bubble continuous positive airway pressure (CPAP) for treatment of children Aged 1-59 months with severe pneumonia in Ethiopia: a cluster randomized controlled clinical trial*

Study code: \_\_\_\_\_ Name: \_\_\_\_\_

Socio-demographic characteristics:

1. Maternal education

- a. illiterate
- b. read & write
- c. <6 grade
- d. 7-8 grade
- e. 9-12 grade
- f. graduate

2. Family size

- a. <5
- b. 5-10
- c. >10

### 3. Monthly income

a. <500br

b. 500-1000 br

c. 1000-2000br

d. >2000br

e. house hold assets

1. Sex: Male ☐ Female ☐ Age (yrs): \_\_\_\_\_ Weight (kg): \_\_\_\_\_  
Height (cm): \_

2. History of presenting illness: Cough -----

Fever -----

Fast breathing/SOB-----

Others specify-----

3. Duration of illness in days-----

4. New-----Repeated----- date of last admission-----

5. Clinical findings

| Parameter          | Admission | 1 hour | 6 hours | 12 hours | 24 hours | 48 hours | 72 hours |
|--------------------|-----------|--------|---------|----------|----------|----------|----------|
| Respiratory rate   |           |        |         |          |          |          |          |
| Nasal flaring      |           |        |         |          |          |          |          |
| Chest indrawing    |           |        |         |          |          |          |          |
| Grunting           |           |        |         |          |          |          |          |
| Cyanosis           |           |        |         |          |          |          |          |
| Consciousness(GCS) |           |        |         |          |          |          |          |
| Oxygen saturation  |           |        |         |          |          |          |          |
| Temperature        |           |        |         |          |          |          |          |

|            |  |  |  |  |  |  |  |
|------------|--|--|--|--|--|--|--|
| Heart rate |  |  |  |  |  |  |  |
|            |  |  |  |  |  |  |  |
|            |  |  |  |  |  |  |  |

5. CXR finding-----

6. HIV status

- a. Negative
- b. Positive
- c. Exposed
- d. Unknown

8. Type of antibiotic started -----

9. Length of hospital stays in days -----

10. Length of stay on bubble CPAP in days-----

11. Outcome of the patient?

- a. Intubated and put on mechanical ventilation
- b. Improved and discharged
- c. Died
- d. Discharged against medical advice

12. Any complications noted

- a. Nasal trauma      yes      No
- b. Nasal obstruction yes      No
- c. Gastric distension yes      No
- d. Pneumothorax      yes      No

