### 5.2 Detailed Description of Methods and Materials

**Stage I.** Testing feasibility, acceptability, and safety of locally constructed bubble CPAP in tertiary care hospitals

**Study Design:** During this Stage feasibility/demonstration stage will be done as a pilot in 3 hospitals where we will evaluate current treatment practice, facilities, and operational challenges for the introduction, clinical use and maintenance of bubble CPAP. Children with severe pneumonia and hypoxemia diagnosed by hospital physician will be enrolled consecutively and put on bubble CPAP. To have this enrolment among the eligible children, we will follow the WHO recommended “Management Algorithm of Children 1-59 months with Acute Respiratory Infections” (Annex 14)

**Study setting:** The study will be conducted at Tikur Anbessa, St. Paul's Millennium and Yekatit 12 Medical College hospitals. The hospitals are located in Addis Ababa, Ethiopia. All the hospitals are tertiary teaching hospitals. An average of 80-100 under five children with severe pneumonia are admitted to St. Paul's Millennium Medical College Hospital & Yekatit 12 hospital and 30-40 patients in Tikur Anbessa Specialized Hospital each month. The current practice of oxygen delivery methods in both hospitals is via low flow oxygen therapy and occasional use of locally constructed bubble CPAP for selected patients based on clinicians' decision. Children with severe pneumonia are also placed on IV antibiotics and other supportive care including maintenance fluid. Children will be placed on mechanical ventilators if they have any specific indication. The indications for mechanical ventilation are acute or chronic respiratory failure, which is defined as insufficient oxygenation, insufficient alveolar ventilation, or both. It can result from several conditions such as pneumonitis (infectious, aspiration), ARDS, cardiogenic pulmonary edema, upper airway obstruction (croup, laryngeal angioedema), lower airway obstruction (severe acute asthma), hypoventilation (drug overdose, Guillain Barre syndrome), severe sepsis and septic shock (25).

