#### **Exclusion criteria**

- Known congenital heart disease, asthma, or upper-airway obstruction
- Tracheostomy

- Pneumothorax
- Needs mechanical ventilation for any specific reason as decided by the clinician

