## Secondary Outcomes

- Death during hospitalization
- Deaths during hospitalization plus within 72 hours of LAMA
- Pneumothorax
- Aspiration pneumonia
- Length of hospital stay
- Incidence of nasal trauma, gastric distention, shock and air leaks
- Duration of bCPAP

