## Sample and sampling procedure:

In this trial, our recruitment goals are approximately a total of 1240 children (620 children each for LF oxygen and bubble CPAP therapy) for a power of 80% and effect size of 50% (reduction of treatment failure, primary outcome of the study, from chart analysis 10% treatment failure in 2019 in comparison facilities) for 12 clusters (103-104 patients in each cluster), adjusted for a intra-cluster correlation coefficient (ICC) level of 0.003 required for cluster randomization. For the calculation of sample size we have used following formula:

Where,  $DF$ , Design effect =  $1 + \delta(m-1)$  [here  $DF=1.52$ ],

$n_1$  = Required minimum sample size per arm,  $\delta$  = the inter cluster correlation,  $m$  = the number of patients in each cluster [103.3 in this study],

$P_1$  = the percentage of treatment failure of children with pneumonia receiving standard treatment (low flow) = 10%,

$P_2$  = the expected percentage of treatment failure of children with pneumonia who will receive intervention (bubble CPAP) = 5% [we have observed 5% treatment failure in two district hospitals during the stage II of our study which correspond 50% effect size],  $Z_\alpha$  = the z-score value [here,  $Z_\alpha = 1.96$  at 5% level of significance],  $Z_\beta$  = the z-score value [here,  $Z_\beta = 0.84$  at 80% power]. We are intending to enroll same number of children (103-104) having our eligibility criteria from each hospital (cluster) irrespective of receiving intervention (bubble CPAP) or standard treatment (low flow).

As a run-in period we will enroll 2 participants in each hospital which will be excluded from final analysis.

**Data collection:** Data will be collected by individual patient assessment through systematic observations using a structured questionnaire. Socio-demographic and different clinical data will be collected. The questionnaire will include the baseline characteristics, intervention and outcome data. All study data will be collected by dedicated study personal at sites.

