## **7. Project Risks and Risk-Management strategies**

This study does not introduce major risks to participants beyond what they would normally face in their condition. As it will be an interventional study with bubble CPAP oxygen therapy, side effects such as nasal trauma, nasal obstruction, gastric distension and pneumothorax are occasionally reported while using bubble CPAP in neonates but such complications are extremely rare in older children. In order to minimize those risks, all the necessary precautions will be taken with routine follow ups. We shall not perform any laboratory investigations for the study purpose except those required for routine care as determined by the hospital clinicians. Breaching medical confidentiality is also a risk. Training and standard SOPs will be implemented to help avoid these problems.

If a significant event caused as a direct result of participation in the study, the study staff will document the incident, inform the site PI, and local medical costs incurred, will be covered by the study's local medical malpractice insurance that is provided by the study.

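### Annex 9 item 12 records gastric distension, nasal trauma and pneumothorax once per stay, with no onset date or status at entry, so new events cannot be told from pre-existing ones

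*Protocol*

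**What the plan says.** Protocol section 5.2, Stage III, Secondary Outcomes, lists "Incidence of nasal trauma, gastric distention, shock and air leaks", with pneumothorax also on a line of its own. The Stage III data analysis paragraph compares primary and secondary outcomes by relative risk with a 95% confidence interval.

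The Stage III data collection paragraph says of the data source: "The questionnaire will include the baseline characteristics, intervention and outcome data". That questionnaire is Annex 9. Its safety item reads "12. Any complications noted" and offers a single yes/no for each of nasal trauma, nasal obstruction, gastric distension ("Gastric distension yes" or no) and pneumothorax. None has an onset date or an entry column.

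The same form has a grid headed "5. Clinical findings", with an admission column and six later time points to 72 hours. It covers nine signs. No row is named for the abdomen, the nose or pneumothorax; two rows are blank. The chest X-ray finding is one undated entry.

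Pneumothorax is a Stage I exclusion that also applies in Stage III. Section 9 provides for separate recording of adverse and serious adverse events under a standard operating procedure.

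**The concern.** An incidence needs two facts per child: that the sign was absent at the start, and that it appeared afterwards. Item 12 supplies neither. A tick shows only that the sign was noted at some point in the stay.

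Two errors could follow. If a share of children in both arms already have the sign at entry, those cases enter numerator and denominator alike and pull the relative risk towards 1. Annex 10 already expects harms to be no more frequent than with low-flow oxygen, so the error would lean towards the expected answer. Second, with six hospitals per arm, entry prevalence may differ between arms by chance, which could create a difference or hide one. The regression adjustment for baseline differences in the Summary cannot help, because it cannot use a variable that was not collected.

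**Working it through.** The protocol states no rate, power or sample size for any safety outcome, so there is no figure of its own to reproduce on this point.

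**What each outcome can show on the form**

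| Outcome | Item 12 | Status at entry | Onset date | Possible at entry? |
|---|---|---|---|---|
| Gastric distension | one yes/no | none | none | yes, not an exclusion |
| Nasal trauma | one yes/no | none | none | less likely, not an exclusion |
| Pneumothorax / air leaks | one yes/no | exclusion only | none; X-ray undated | only if undetected |
| Shock, aspiration pneumonia | no field | – | – | – |

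**Illustration.** Inputs from the protocol: 620 children per arm, 103.3 per hospital, intra-cluster correlation 0.003. Every event rate and entry prevalence below is an assumption.

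Let *b* be entry prevalence and *c* the new-onset risk. The recorded risk is *b* + (1 − *b*)*c*.

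With *c* = 2% on low flow and 4% on bubble CPAP (true relative risk 2.0) and *b* = 5% in both arms:
- low flow: 0.05 + 0.95 × 0.02 = 0.069
- bubble CPAP: 0.05 + 0.95 × 0.04 = 0.088
- recorded relative risk: 0.088 / 0.069 = 1.28

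For power, the design effect from the protocol's correlation and cluster size is 1 + 0.003 × 102.3 = 1.307, so the effective number is 620 / 1.307 ≈ 474 per arm. (The protocol prints 1.52, which does not follow from those two inputs; a larger design effect would lower every power below.)

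| Entry prevalence, both arms | Recorded RR | Risk difference (points) | Approximate power |
|---|---|---|---|
| 0% | 2.00 | 2.00 | 44% |
| 1% | 1.66 | 1.98 | 35% |
| 2% | 1.49 | 1.96 | 29% |
| 5% | 1.28 | 1.90 | 19% |
| 10% | 1.15 | 1.80 | 13% |

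With a 5% control risk and a true relative risk of 2, prevalences of 5% and 10% give recorded values of 1.49 and 1.31, and power falls from 83% to 61% and 46%.

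**Imbalance with no true harm** (2% new onset in both arms):
- entry prevalence 6% v 4%: (0.06 + 0.94 × 0.02) / (0.04 + 0.96 × 0.02) = 0.0788 / 0.0592 = 1.33
- entry prevalence 8% v 4%: (0.08 + 0.92 × 0.02) / 0.0592 = 0.0984 / 0.0592 = 1.66

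**The case against.** A reader might infer that conditions present on admission are being counted as harms. The protocol does not say so. Item 12 asks about complications, and the outcome list speaks of incidence, so the intention is new events. What stands is that the form cannot confirm it.

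A reader might also extend the point to all safety outcomes, shock and aspiration pneumonia included. Those two have no field in item 12, so they cannot be recorded there as an undated yes/no; their absence is a different gap. Nor does the list beginning "It can result from several conditions such as pneumonitis (infectious, aspiration), ARDS" show that such conditions are common at entry. It explains why children need mechanical ventilation, and children who need it are excluded. The statement "We shall not perform any laboratory investigations for the study purpose except those required for routine care" concerns laboratory tests and does not settle whether a chest film precedes entry.

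The separate adverse event record is the best counter-argument. Section 9 sets a 48-hour deadline for reporting serious events to the regulator, and section 6 a 24-hour deadline for telling the safety board about severe ones; both presuppose a known onset. Its form is not shown and may carry dates. But the general record is limited to events linked to trial participation, the deadlines cover only serious or severe events, and nothing makes this record the source of the listed secondary outcomes.

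Three further limits stand. The illustrated sizes rest wholly on assumed rates. The risk difference hardly moves under equal prevalence, although the protocol specifies relative risk. Power is only 44% for 2% v 4% even with perfect data, so sample size is the larger obstacle there. A counting rule could sit in an analysis plan that is not shown, but no analysis plan can restore an entry status that was never recorded.

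**Conclusion.** The point holds in limited form. The outcome list asks for incidence, the questionnaire is the named data source, and it does not record what is needed to tell new gastric distension or nasal trauma from pre-existing. It is strongest for gastric distension, weaker for nasal trauma, and for pneumothorax covers only cases undetected at entry that an undated film cannot place in time.

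The consequence is conditional. At zero entry prevalence there is no bias, but the form could not show that it was zero. Over an assumed 0% to 10%, a true relative risk of 2 is recorded as anything from 2.00 to 1.15 (2% control risk) or 2.00 to 1.31 (5% control risk). The primary outcome, allocation and main analysis are untouched. It is a worthwhile improvement because it is cheap and the missing information cannot be reliably recovered after discharge.

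**What to change.** In Annex 9 item 12, give each complication an at-enrolment yes/no and a date and time of first onset. Put a date and time on the chest X-ray finding. In Secondary Outcomes (Stage III), state that only events first seen after study oxygen starts, in children free of them at enrolment, are counted. Entry prevalence by arm can then be tabulated beside the relative risks.

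The cost is slightly more data entry on an existing form and one sentence in the outcome section. No extra visit, test or staff is needed.

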|                       | 
Secondary outcomes:
 
 
• Death
 
• Adverse events (pneumothorax, abdominal distension, nasal trauma, aspiration pneumonia) encountered.
 
                                                                                                                                                                                                                                                                                                                                                                                                                                                                                                                                                                                                                                                                                                                                                                                                                                                                        |
| Research Sites | St. Paulos Millennium Medical College, Yekatit 12 and Tikur Anbessa Specialized hospitals, 14 district hospitals                                                                                                                                                                                                                                                                                                                                                                                                                                                                                                                                                                                                                                                                                                                                                                                                                                                                                                                                                     |

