|                                        | 
pneumonia and hypoxemia
 
 
- To record adverse events (pneumothorax, abdominal distension, nasal trauma, aspiration pneumonia) encountered.
 
                                                                                                                                                                                                                                                                                                                                                    |
| Number of Participants/Patients | 
Stage I-30 children in each tertiary hospital
 
Stage II- 20 children in each general hospital (2 general hospitals)
 
Stage III-620 children in each arm of the study (6 hospitals in each arm)
                                                                                                                                                                                                                                                                                                                                    |
| Main Inclusion Criteria         | 
 
- Age between 1 month and 59 months
 
-Meet WHO clinical criteria for severe pneumonia with hypoxemia
 
-Hypoxemia (Oxygen saturation <90% in room air)
 
-Parent/guardian gives informed consent to participate in the study
 
                                                                                                                                                                                                                                              |
| Statistical Analysis            | 
A descriptive analysis of data of stages I and II will be performed to assess the level of feasibility and acceptability both at provider and patient levels
 
 
- In stage III we shall follow the principle of intention to treat (all children enrolled in the study will be included in the analysis irrespective of whether they have completed the study intervention). Primary and secondary outcomes will be analyzed using <math>\chi^2</math> or Fisher's exact tests as appropriate.
 
 |

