|                                                   |                                                                                                                                                                                                                                                                                                                                                                                                                                                                                                                                                                                                                                              |
|---------------------------------------------------|----------------------------------------------------------------------------------------------------------------------------------------------------------------------------------------------------------------------------------------------------------------------------------------------------------------------------------------------------------------------------------------------------------------------------------------------------------------------------------------------------------------------------------------------------------------------------------------------------------------------------------------------|
|                                                   | 
-Continuous variables will be analyzed using the Student t-test or the Mann-Whitney test as appropriate.
 
-The primary outcome of the study is treatment failure and the secondary outcomes are death, pneumothorax, abdominal distention, nasal trauma, aspiration pneumonia.
 
-Primary and secondary outcomes will be compared by calculating relative risks (RRs) and their 95% confidence intervals.
 
- Log-linear binomial regression will be applied to adjust for covariates to evaluate the true impact of bubble CPAP in evaluating primary and secondary outcomes and to adjust for baseline differences.
 |

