On the basis of knowledge gap found from the systematic review in treating children with severe pneumonia and hypoxaemia with bubble CPAP especially in children beyond neonatal period, the Bangladesh trial was conducted which found a beneficial effect of bubble CPAP in these children. The trial done in Bangladesh showed that, among the children who received bubble CPAP for the treatment of severe pneumonia some children developed abdominal distension, and nosocomial infection, however, these adverse events were similarly observed with WHO standard low flow oxygen therapy in the same trial [11]. It is also important to note that bubble CPAP has been used routinely to support nearly 1,000 children with severe pneumonia and hypoxemia at the icddr,b hospital in Bangladesh with beneficiary outcome almost consistent with the trial outcome [24].

After the end of Bangladesh trial, an observational prospective study done in 77 Malawian children (1 week to 14 years) with progressive acute respiratory failure revealed that forty-one (53%) patients survived following bCPAP treatment, and an HIV-uninfected single-organ disease subgroup demonstrated bCPAP success in 14 of 17 (82%) [25].

Another prospective study, conducted in the Pediatric Emergency Unit of a teaching and referral hospital in North India which included 330 children (110 put on bubble CPAP) with clinical pneumonia and hypoxemia aged 1 month–12 years, they compared bubble CPAP with low flow oxygen and revealed that fifty-three children (25.9%) on low flow oxygen therapy were shifted to bCPAP for worsening distress and hypoxemia. There were a total of nine deaths (2.7%) in the study cohort; all deaths occurred in intubated children, of which only one child was initially in bCPAP group [26].

Another study done in 120 children under 2 years with moderate to severe lower respiratory tract infection revealed that bubble CPAP was successful in 72% of children [27].

A recent literature review which included 45 studies (17 clinical trials, 11 literature reviews, 10 technical assessment, three reports of real world implementation in low resource settings, three cost analysis, one case report) also concluded that CPAP is a safe and effective method of treating infants and young children with life threatening respiratory distress and can be successfully adapted for use in resource limited settings [28].

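### Aspiration pneumonia and shock are Stage III secondary outcomes, but the Annex 9 questionnaire has no field for either, so their capture may be incomplete and may differ between arms

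*Protocol*

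**What the plan says.** Aspiration pneumonia appears in four places in the protocol. The Summary gives a Stage III objective, "To record adverse events (pneumothorax, abdominal distension, nasal trauma, aspiration pneumonia) encountered", and a matching secondary outcome, "Adverse events (pneumothorax, abdominal distension, nasal trauma, aspiration pneumonia) encountered". Its statistical analysis row states that "the secondary outcomes are death, pneumothorax, abdominal distention, nasal trauma, aspiration pneumonia". The Stage III list under Secondary Outcomes has "Aspiration pneumonia" as its own entry.

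Shock and air leaks appear only in that last list, as "Incidence of nasal trauma, gastric distention, shock and air leaks". The Summary and the Stage III data analysis paragraph both promise relative risks with 95% confidence intervals for secondary outcomes.

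On data capture, the Stage III methods describe a structured questionnaire and say: "The questionnaire will include the baseline characteristics, intervention and outcome data". Annex 9 is headed as the questionnaire. Its item 12, "Any complications noted", has four yes/no lines: nasal trauma, nasal obstruction, gastric distension and pneumothorax.

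Two other sections deal with events. Section 9 has staff document adverse and serious adverse events linked to taking part in the study. It also sends every serious adverse event, related or not, to the regulator within 48 hours, with quarterly summaries. Section 6 sends severe adverse events and deaths to the DSMB within 24 hours.

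**The concern.** The outcome list and the form do not match. Two complications that the trial undertakes to compare between arms are not asked about on the form that is meant to hold the outcome data. An analysis plan cannot repair this later, because it cannot recover an answer that was never sought.

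At stake is part of the safety comparison. If a child's form is silent on aspiration or shock, the analyst cannot tell whether the event did not happen or nobody was asked. A relative risk built on such data depends on how events happened to reach another reporting route, and that may differ between hospitals and between arms.

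**Working it through.** The protocol gives no figure to reproduce. The check sets the outcome list against the form, and then looks for any other place where the missing items could be found.

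**Step 1. Outcome list against item 12.**

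| Complication in Stage III Secondary Outcomes | Field in Annex 9 item 12 |
|---|---|
| Pneumothorax | Yes |
| Nasal trauma | Yes |
| Gastric distension | Yes |
| Air leaks | Only through pneumothorax |
| Aspiration pneumonia | None |
| Shock | None |

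Item 12 has no open line, although the presenting-illness item on the same form has one.

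**Step 2. Could another field on the form supply them?**
- Shock: the clinical table has heart rate and consciousness, but no named row for blood pressure or perfusion. Two rows are blank. The table runs from admission to 72 hours.
- Aspiration pneumonia: there is one undated free-text line for the chest X-ray. Every enrolled child has severe pneumonia at entry, so this line cannot separate a new aspiration event from the presenting illness.
- The final-outcome item offers ventilation, improvement, death or discharge against advice, and identifies neither event.

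**Step 3. Could the other reporting routes supply them?**
- General adverse events (section 9) are documented when associated with participation, which requires a causal judgement. Low-flow oxygen is the existing standard in district hospitals, bubble CPAP is new there, treatment is visible, and whole hospitals belong to one arm. The judgement may therefore be made differently by arm.
- Serious adverse events are reported regardless of relation, but to the regulator. Severe events and deaths go to the DSMB. The protocol does not say that either stream feeds the comparative analysis.
- None of these routes gives a yes or no for each child.

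**Step 4. Effect on the estimate.** Let *p* be the true risk in an arm and *c* the probability that an event is captured there, with no false reports. Then:

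observed risk = *c* × *p*

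observed relative risk = (*c*₁/*c*₀) × true relative risk

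If *c*₁ = *c*₀ < 1, both rates are understated and the relative risk is unchanged on average, though less precise. If *c*₁ ≠ *c*₀, the relative risk is distorted by the ratio *c*₁/*c*₀. The protocol fixes neither value, so the direction is unknown.

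**Step 5. Scale.** The protocol gives no incidence for either event. With an assumed incidence of 1% to 3% and 620 children per arm, 0.01 × 620 = 6.2 and 0.03 × 620 = 18.6. So roughly 6 to 19 events of each type per arm would have no structured field. That is not a count of lost events, since some would reach the routes in step 3.

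**The case against.** The strongest reply is that other recording exists. Shock in a hypoxaemic child would plausibly be serious, and aspiration pneumonia often would be. Such events are reportable whether or not they are judged related. This stands, and it limits the point.

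A reader might infer from the form that the trial would record no aspiration pneumonia or shock at all, that 0 of 620 per arm would be reported whatever the truth, and that the rule of three would then give an upper limit of 3/620 = 0.48%. Sections 6 and 9 do not support that reading. A question never asked also gives missing data, not zero events in 620 children, so no confidence limit follows. Nor does the protocol show that a false finding of no risk would result.

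Some annex pages were not available for this review, section 9 refers to a standard operating procedure that is not shown, and the protocol speaks of data collection tools in the plural. A separate adverse-event form cannot be ruled out. Even so, the mismatch between Annex 9 and the outcome list would still need to be reconciled.

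Two further criticisms would go too far. Section 1.5 says of the earlier Bangladesh trial that "some children developed abdominal distension, and nosocomial infection", but it adds that these events occurred similarly on low-flow oxygen, and nosocomial infection is not an outcome here. Its absence from the form is not an inconsistency. Nasal obstruction is on the form without being a listed outcome, but section 7 names it as a known side effect, and collecting it does no harm.

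**Conclusion.** The mismatch is confirmed. Two named Stage III secondary outcomes, aspiration pneumonia and shock, have no field on the only data form seen, and air leak other than pneumothorax has none either. The supportable consequence is unsystematic capture that may depend on arm, so rates may be understated and relative risks may not be comparable.

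The size of this cannot be derived from the protocol, because it depends on unknown incidences and capture probabilities. Only secondary outcomes are touched; the primary outcome does not depend on item 12. The conclusion assumes that Annex 9 is the questionnaire meant in the Stage III methods and that no unseen form asks about these events for every child. The change should be made, because it costs little and the information cannot be recovered afterwards.

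**What to change.** Either of two changes would settle it:

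1. Add yes/no fields to Annex 9 item 12 for aspiration pneumonia (new after enrolment), shock, and air leak other than pneumothorax. Each needs a short case definition and an onset date, and must be identical in both arms. The definition matters most for aspiration pneumonia, because all children enter with pneumonia and undefined boxes would not give comparable counts across hospitals.
2. Alternatively, state that these outcomes are taken from the adverse-event record, and that this record is completed for every child in both arms regardless of attribution.

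In either case, make the adverse-event outcome lists in the Summary (objectives, secondary outcomes and statistical analysis) agree with the Stage III Secondary Outcomes. Nasal obstruction can stay on the form.

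The cost is a few extra fields and a short amendment. No extra tests are needed, since events would be recorded as diagnosed in routine care.
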